##### d.2. Longitudinal models

In order to analyse the changes of an outcome variable with time, longitudinal (or panel) data models will be estimated. The estimated models belong to the family of generalised linear mixed models (GLMMs). The link function and distribution of error terms will be defined depending on the nature of the dependent variable. In the GLMMs models, only the intercept will be specified as random in order to capture repetition of data across individuals. It will also be possible to account for various levels of heterogeneity across countries by including country specific random effects (multilevel model). Time-fixed effects will be included in the model to assess changes of a dependent variable over time, and interactions between time-fixed effects and regressors of interest will be included to test for changes in the impact of a variable over time. Potential attrition bias will be assessed and accounted for using the methods described above (missing data management).

## Appendix 2

Table

**Table 1 Tab1:** Summary of objectives, statistical analyses and tools

Objective	Tools	Timing	Analysis
Assess the psychological impact of risk communication on women	- STAI (Q1) - Lerman’s cancer worry (Q2) - Qualitative interviews	Baseline, 3 months, 1 year, 4 years	- Comparisons between two experimental arms, controlling for baseline levels and other covariates where required
Assess women’s comprehension of the information provided within MyPeBS, and their willingness to search for further information	- Comprehension questionnaire (Q3) - Information seeking behaviours questionnaire (Q4) - Qualitative interviews	Baseline, 3 months, 4 years	- Comparisons between arms and correlations between women’s information comprehension level, information-seeking behaviours and socio economic and demographic characteristics - Correlations with psychological characteristics (anxiety, cancer worry)
Analyse MyPeBS participants' socio-economic and demographic characteristics as well as quality of life	- Quality of life (Q6) - Socio-demographic questionnaire (Q8)	Baseline, 4 years	- Comparisons between arms of women’s socio-economic characteristics and quality of life, focus on health inequalities. Use equality of proportion or Student test to compare the distribution of the variables across the two harms - Correlations with risk perceptions and screening uptake
Assess perception of risk of breast cancer, and perceptions of efficacy and risks of prevention options	- Risk perception and behaviour change (Q5) - Information-seeking behaviour questionnaire (Q4) - Qualitative interviews	Baseline, 3 months, 4 years	- Comparisons between two experimental arms, controlling for baseline levels and other covariates where required - Examination of mediation effects on intentions and behaviour by risk appraisals and coping appraisals
Measure overall satisfaction with the trial and acceptability of the risk-based approach	- Trial Program Satisfaction (Q7) - Qualitative interviews	1 year, 4 years	- Comparison between arms and analysis of critical points within experimental arm

1

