### Procedure

Psychosocial questionnaires (see Fig. 1) are administered on the web platform to women at different times during the trial, namely at inclusion (baseline), at three months, at one year and at four years (end of trial). Women complete the baseline psycho-social and medical questionnaires before the randomisation process. Both steps are performed by the recruiter during the inclusion visit. For each other stage of the trial, women receive an invitation by email to complete the next questionnaires. Participants are given a one-month window and receive weekly email reminders to complete the three-months form online. At one year and four years, they are given a two-months window and bi-monthly reminders to fill in the forms. The study sponsor (Unicancer) is responsible for data management and ensures quality control, storage and exportation of data for dedicated analyses.

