#### State-Trait Anxiety Inventory (STAI) (Q1) and Lerman Cancer Worry scales (Q2) (at baseline, three months, one year and four years)

In order to assess if increased distress is a harm of risk-stratified breast cancer screening, the research team will compare the levels of general anxiety and cancer-specific worry between women who receive risk-stratified screening and women who receive standard screening. Cancer-specific worry measures seem to be more sensitive to the effects of receiving risk information than more general measures of anxiety [30, 31]. By contrast, there is evidence that more general measures of anxiety are better linked to diagnoses of psychological disorders [32]. For this reason, we assess both indices of psychological distress, using standardised measures, namely the short form State-Trait Anxiety Inventory (STAI) to assess general state anxiety [33] and the Lerman cancer-worry scale to assess cancer-specific worry [34].

The Lerman Cancer worry scale questionnaire has been used in similar studies evaluating cancer risk assessment and clinical programmes [22, 35]. The STAI short form questionnaire is a validated questionnaire which has been implemented across many studies, including breast cancer risk-stratification research [22]. Both scales have six items with four response options each. Composite scores are then calculated, with score ranges between 4 and 24, with higher scores indicating higher anxiety.

There is also evidence that both general anxiety and cancer-related worry peak shortly after receiving information on cancer risk and then gradually decline [30, 31]. For this reason, we will assess these variables over time and across the six countries, to examine whether there are short-term increases as well as any longer-term effects.

As levels of anxiety might be affected if women have their mammogram the day they fill in those questionnaires, information on whether or not a mammogram is planned on the day of inclusion will be collected.

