#### Risk perception and behaviour change (Q5) (at baseline, three months, and four years)

As previously underlined, it is essential that all decisions made as part of breast cancer screening are informed and based on sound understanding of good quality information provided. A key element of understanding is how accurately women perceive their own risk of breast cancer following risk-stratified screening, and whether this has been improved, relative to standard screening. For these reasons, we will assess perception of risk of breast cancer, and perceptions of efficacy and risks of different prevention options, to assess the constructs of Protection Motivation Theory, a theory that aims to understand how risk information can translate into behaviour change or not [45]. Uptake of options that may reduce future risk of breast cancer such as increased frequency of mammography in women at high risk, or increases in healthy eating or physical activity, is linked to perceptions of the risk of disease and benefits of these behaviours in reducing risk [11]. By contrast, a potential harm of risk-stratified screening is that those who are told they are low risk may increase their unhealthy behaviours through being falsely reassured (i.e., a certificate of health effect).

To estimate comparative risk and comparative severity scores, participants are asked to choose a category indicating their perceived risk of invasive breast cancer over the next ten years, compared to the population’s average (comparative risk). They are also asked to evaluate, if they were to get breast cancer, how severe they think this would be (comparative severity) on a five-point scale from lower to higher risk.

The behaviour change questions evaluate three different behaviours relating to reducing breast cancer risk: improving diet, increasing physical activity and attending mammography appointments. Five-point scales are used to measure Response Efficacy (the perception of how much the behaviour would reduce the participant’s risk of breast cancer) and Self-Efficacy (how easy or difficult it would be to enact these behaviours). To calculate the intention to change behaviour scores, participants are asked three questions assessing their intention to change the three health-related behaviours on a five-point scale, from “strongly disagree” to “strongly agree” [22].

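### The random-intercept-only rule for the longitudinal models forces equal correlation across unequally spaced waves and can misstate standard errors of change for outcomes with three or more waves

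*Protocol article*

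**What the plan says.** Section d.2 of Appendix 1 places the longitudinal models in the generalised linear mixed family: "The link function and distribution of error terms will be defined depending on the nature of the dependent variable". On dependence within a woman it gives one rule: "only the intercept will be specified as random in order to capture repetition of data across individuals". The only extension it allows is an optional random effect for country. Change over time is tested through categorical time effects, and "interactions between time-fixed effects and regressors of interest will be included to test for changes in the impact of a variable over time".

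No random slope, residual correlation structure or robust variance is named for these models. Heteroscedasticity-consistent errors appear only in section d.1, for the cross-sectional linear models.

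The Procedure section sets waves at baseline, three months, one year and four years. By the headings under Measures:
- Q1 (STAI) and Q2 (Lerman) are collected at all four waves.
- Q3 and Q5 are collected at baseline, three months and four years. The closing text on Q3 mentions only the two later waves.
- Q4, Q6 and Q7 are collected at two waves each.

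**The concern.** In a linear mixed model with independent residuals, a lone random intercept implies that any two measurements on the same woman correlate equally, whatever the time between them. Here successive waves lie 3, 9 and 36 months apart. Scores three months apart would ordinarily correlate more strongly than scores four years apart. The section on Q1 and Q2 also expects distress to rise soon after risk information and then subside, and it wants both short-term and longer-term effects examined.

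Those questions concern differences between waves, and the standard error of such a difference depends directly on the correlation of the pair. If one common correlation is imposed, the model averages over pairs. It then overstates uncertainty for close waves and understates it for distant ones. The risk that matters more is the second: four-year effects declared with more confidence than the data support. A large sample does not cure this, because the ratio of model to true standard error does not depend on n.

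**Working it through.** **The plan's own figure.** The sample size section claims over 99% power for a standardised difference of 0.08 with 70% follow-up of 22,000 women. 22,000 × 0.70 = 15,400, or 7,700 per arm. SE = √(2/7,700) = 0.0161; 0.08/0.0161 = 4.96; 4.96 − 1.96 = 3.00; power 99.87%. The claim reproduces. It is a single-time comparison and does not involve the mixed model.

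**Formula.** Take unit variance at each wave, n women per arm, complete data, and categorical time crossed with arm.
- True variance of the arm difference in change from wave s to wave t: 2(1 − ρ_st) × 2/n.
- The random-intercept model uses the average correlation ρ̄ for every pair: 2(1 − ρ̄) × 2/n.
- Model SE / true SE = √[(1 − ρ̄)/(1 − ρ_st)].
- Actual two-sided type I error = 2[1 − Φ(1.96 × ratio)].

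**Assumed correlations** (none are in the documents), in the order 0–3, 0–12, 0–48, 3–12, 3–48, 12–48 months:
- Mild decay: 0.65, 0.60, 0.50, 0.65, 0.55, 0.60; ρ̄ = 3.55/6 = 0.592
- Moderate decay: 0.70, 0.60, 0.40, 0.65, 0.45, 0.50; ρ̄ = 3.30/6 = 0.550
- Steep decay: 0.80, 0.60, 0.30, 0.70, 0.35, 0.40; ρ̄ = 3.15/6 = 0.525

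Example, moderate decay, baseline to 48 months: √(0.450/0.600) = 0.866; 2[1 − Φ(1.697)] = 9.0%.

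**Four waves (Q1, Q2): SE ratio and type I error**

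| Decay | 0→3 | 0→12 | 0→48 |
|---|---|---|---|
| Mild | 1.08; 3.4% | 1.01; 4.8% | 0.90; 7.7% |
| Moderate | 1.22; 1.6% | 1.06; 3.8% | 0.87; 9.0% |
| Steep | 1.54; 0.25% | 1.09; 3.3% | 0.82; 10.6% |
| Equal correlation | 1.00; 5.0% | 1.00; 5.0% | 1.00; 5.0% |

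**Three waves (Q3, Q5 treated as scores; ρ̄ = 0.567, 0.517, 0.483)**

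| Decay | 0→3 | 0→48 |
|---|---|---|
| Mild | 1.11; 2.9% | 0.93; 6.8% |
| Moderate | 1.27; 1.3% | 0.90; 7.9% |
| Steep | 1.61; 0.2% | 0.86; 9.2% |

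**Two waves (Q4, Q6, Q7).** There is only one correlation, so ρ̄ = ρ_st and the ratio is 1.00 in every scenario.

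**Sensitivity to the assumptions.** A second four-wave set, with baseline correlations 0.65/0.60/0.50, 0.70/0.60/0.40 and 0.75/0.60/0.30 and lower averages (0.565, 0.532, 0.503), gives:
- 0→48: √(0.435/0.50) = 0.93, √(0.468/0.60) = 0.88 and √(0.497/0.70) = 0.84; type I error 6.8%, 8.3% and 9.9%.
- 0→12: √(0.435/0.40) = 1.04, √(0.468/0.40) = 1.08 and √(0.497/0.40) = 1.12.

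**Check by fitting the model.** A random-intercept model was fitted to one simulated data set with moderate decay and 3,000 women per arm. It gave 0.0244 as the SE of every change. The true values are 0.0200 (0→3), 0.0231 (0→12) and 0.0283 (0→48), so the ratios are 1.22, 1.06 and 0.86. With two waves and unequal SDs (1 and 1.3) the ratio was 1.00.

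**The case against.** **Arm comparisons have another route.** Section c of Appendix 1 tests two-group differences in quantitative variables by ANCOVA on baseline, and Appendix 2 describes the distress objective as arm comparisons controlling for baseline. A single-wave ANCOVA does not use the mixed-model covariance. Section d.2 also interacts time with regressors of interest without naming arm. This stands and limits the reach of the point. It does not remove it, because d.2 is where the plan places inference on change over time, and tests of time effects alone rest on the same covariance.

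**The rule limits random effects only.** Read strictly, it bars random slopes, and a serially correlated residual or a robust variance would be compatible with it. That is fair. But the sentence presents the random intercept as the means of handling repeated data, and d.1 shows that robust errors are named where they are intended. Followed as written, the rule gives equal correlation.

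**Stronger readings.** A reader might infer that every arm-by-time contrast is wrong. The schedule does not support this: two-wave outcomes are unaffected, the change to one year (the time the Objectives name for distress) is off by only about 1% to 12%, and nothing is wrong if correlations are in fact equal.

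A reader might also infer that the expected three-month peak would be missed. At the plan's own 7,700 per arm and a difference of 0.08 it would not. Under moderate decay the model SE is √(4 × 0.45/7,700) = 0.0153 and the true SE is √(4 × 0.30/7,700) = 0.0125. Then (0.08 − 1.96 × 0.0153)/0.0125 = 4.0, so power exceeds 99.9%. France does not receive Q1 and Q2 and its share is not stated. If that halved the sample (an assumption), the value becomes 2.13 and power is still about 98%.

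The country random effect adds no further fault here. It is optional and does not alter how correlation varies with the gap.

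**Conclusion.** The concern holds in a limited form. For quantitative outcomes with three or more waves, the intercept-only rule imposes a correlation pattern that is unlikely with gaps of 3 to 48 months.
- Baseline to four years: standard errors about 7% to 18% too small, type I error about 7% to 11%.
- Baseline to three months: about 8% to 54% too large with four waves, and up to about 61% with three. Tests are conservative.
- Baseline to one year: nearly right to about 12% too large.

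The direction rests on correlation falling with the gap. The sizes rest on assumed correlations, equal variances across waves, complete data and a linear model. The documents supply no correlations, so the sizes are illustrative. Q3 is affected only if it is collected at three waves, as its heading says. The plan's power statement is not affected.

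**What to change.** In section d.2, replace the intercept-only rule for quantitative scores with three or more waves by an unstructured within-woman covariance over the waves. The participant random intercept is then dropped for those scores, since the covariance already carries the dependence. For binary or ordinal outcomes, keep the mixed model and state that standard errors are robust and clustered on the woman. For quantitative scores the unstructured covariance is preferable to robust errors alone: with incomplete follow-up, the estimates as well as their standard errors lean on the covariance being right.

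The cost is a sentence or two in the plan. Four waves need 4 variances and 6 covariances, ten parameters in all; three waves need six. With thousands of women this is negligible, and almost nothing is lost if the correlations prove equal. The ANCOVA comparisons and the two-wave outcomes need no change.

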#### Quality of life (Q6) (at baseline and four years)

To assess women’s quality of life, we use the EQ-5D licensed by EuroQoL research foundation. This European quality of life tool is a validated pre-scored multi-attribute health status scale that has been used in a wide range of populations and situations, including breast cancer screening [46–49]. It is short and easy to complete. It is divided into two parts: a first part with five items representing five dimensions, i.e. mobility, self-care, usual activities, pain and discomfort, anxiety and depression. The patient is asked to respond on a five-point scale: 1, no problem; 2, mild problems; 3, moderate problems; 4, severe problems; 5, extreme problems or total disability. A second part with a visual analog scale “EQ-5D VAS”, a 20-cm line graduated from 0 to 100 allows the patient to rate his or her current health status, with 0 being the worst health status and 100 the best.

The EQ-5D is administered at baseline and at four years to analyse and compare women’s quality of life between the two screening options, i.e. standard versus personalised breast cancer screening, and between groups of different risk levels. We will thus explore whether women who underwent risk-stratified screening have a better quality of life than women who underwent standard screening. Quality of life among different socio-economic subgroups will also be compared and related to breast cancer screening compliance, using both aggregated and unaggregated measures (i.e. considering the five dimensions of the EQ-5D separately) of quality of life, based on the responses to the EQ-5D questionnaire.

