### Analyses

The quantitative analysis plan (see Appendix 1) includes: 1) descriptive statistics (description of categorical and quantitative variables, tests and estimation of confidence intervals); 2) bivariate analyses, subgroups comparisons and analysis of variations in time (baseline, three months, one year and four years), with appropriate tests to assess differences in groups (e.g. chi-square, Fisher and Student, Q Cochran); 3) multivariate regression models (cross-sectional and longitudinal) to model different patient reported outcomes such as comprehension of the information provided, general anxiety or cancer worry, and information-seeking behaviours. The data management and statistical analyses will be performed using Stata (StataCorp LP) and SPSS (IBM Corp). The main endpoint of this study will be measured at the end of the four years of intervention.

The qualitative data will support the interpretation of findings from the quantitative data. It will use framework analysis, a form of thematic analysis that facilitates the handling of large qualitative datasets [53]. It involves examining qualitative data to produce themes that summarise and interpret patterns of results. The analysis will take an explicit comparative approach, to investigate differences between England and France, and will also consider how the level of estimated risk affects reactions to risk-stratified screening and how acceptable the women found this. Coding will continue until the team is satisfied that codes and themes adequately describe and capture the data and that saturation has been achieved. Data will be stored and organised within Nvivo software (QSR International Pty Ltd. Version 12, 2018).

Dissemination of the study results will include the publication of research papers. A more direct feedback to investigators and to participants is planned at various stages of the trial.

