## Discussion and conclusion

As of December 31^st^, 2021, 22,884 participants have been included and randomised in the trial and have completed baseline questionnaires. Inclusion for the qualitative study started in November 2021 in France and will start in March 2022 in the UK.

The Covid crisis resulted in a six-months suspension of trial enrolment as of March 2020, and still has a major detrimental impact on the recruitment, as successive epidemic waves continue to hinder both women and healthcare teams to participate in the study. Furthermore, when the enrolment reopened, one of the priorities was to reduce participants' time on site as much as possible. It was therefore decided to have women complete the first two questionnaires (STAI and Lerman cancer worry scale) at the inclusion site prior to randomisation, while the other questionnaires could be completed afterwards, either at the inclusion site or at home. This allowed the scientific requirements for assessing anxiety levels to be maintained prior to the start of the study, while adapting the conditions of inclusion to the health context.

One point to note is that the French Ethics committee limited the range of questionnaires proposed to women in France, due to concerns around heightened anxiety after answering the STAI-6 (Q1) and Lerman cancer worry scale (Q2). These questionnaires, however, will be administered in the five other countries taking part in the trial.

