#### c. Bivariate analyses and subgroups comparisons

The bivariate analyses will mainly focus on detecting differences between subgroups (e.g., countries). Before, it will be ensured that each group contains a sufficient number of participants and is adequately powered.

For the qualitative or discrete variables, the significant differences between subgroups will be assessed either by means of the Chi-square test or by Fisher's exact test depending on the conditions of statistical validity (i.e., theoretical number strictly less than 5).

The Cochran Mantel Haentszel test (or Q Cochran) will test for equality of proportions in matched samples. It will be used to test, for instance, how the comprehension level of risk stratified screening varies in time, (i.e., between baseline, three months and four years).

For quantitative variables, significant differences between two subgroups will be detected via Analysis of Covariance (ANCOVA), controlling for baseline levels of those variables, and any other clinical or demographic variables that are not well balanced between subgroups, and hence may have a confounding effect. Initial assumption testing will include the Fischer test, which will be used to verify the hypothesis of equality of variances, and the Shapiro Wilk test, which will be used to verify the hypothesis of normality. In the case of non-normality, non-parametric approaches will be used in sensitivity analyses. In this case, the Wilcoxon or Mann–Whitney test for comparisons between two subgroups and the Kruskal–Wallis test beyond two subgroups will be considered.

The tests will be bilateral with a significance level of 5%. Adjustments for multiple comparisons (Bonferroni correction) do not appear to be required.

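### For the continuous EQ-5D measures, Table 1 names an unadjusted Student test between arms where Appendix 1 prescribes ANCOVA on baseline; the two should be reconciled

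*Protocol article*

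**What the plan says.** Three places in the protocol article bear on how quality of life is compared between arms.

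- **Appendix 2, Table 1, objective 3.** The row covers the EQ-5D (Q6) and the socio-demographic questionnaire (Q8), at baseline and four years. Its analysis column reads: "Use equality of proportion or Student test to compare the distribution of the variables across the two harms" (the last word is evidently a slip for arms). No baseline covariate is mentioned.
- **Appendix 1, section c.** For quantitative variables, "significant differences between two subgroups will be detected via Analysis of Covariance (ANCOVA), controlling for baseline levels of those variables". For qualitative or discrete variables, "the significant differences between subgroups will be assessed either by means of the Chi-square test", or by Fisher's exact test where expected counts are small.
- **Appendix 2, Table 1, objectives 1 and 4.** Both rows say: "Comparisons between two experimental arms, controlling for baseline levels and other covariates where required".

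A baseline value exists: "The EQ-5D is administered at baseline and at four years", and the Quality of life section gives comparison of the two screening options as a purpose. That section describes a 0 to 100 visual analogue scale, five separate dimensions, and aggregated as well as dimension-level use of the responses.

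**The concern.** The VAS and an EQ-5D index are quantitative. Under Appendix 1 they would be compared by ANCOVA with the baseline value as covariate; under the objective 3 row, by a two-sample Student test. The two analyses estimate the same difference in means with different standard errors and can give different p-values. Testing is two-sided at 5%, and Appendix 1 sees no need for multiplicity adjustment, so an unresolved choice between two tests for one outcome is better closed before the four-year data are seen.

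Precision is also at stake. Wherever baseline EQ-5D predicts four-year EQ-5D, the Student test leaves explainable variance in the error term and chance baseline imbalance in the estimate.

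**Working it through.** **Inputs from the documents.** Sample size justification: 70% follow-up of the first 22,000 women, a standardised mean difference (SMD) of 0.08, and power stated as over 99%. Background: 1:1 randomisation. Appendix 1, section c: two-sided 5% level.

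**Assumed input.** The correlation r between baseline and four-year EQ-5D is not given. I take 0.4, 0.5 and 0.6.

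**Step 1: the plan's own figure.** Followed women: 22,000 × 0.70 = 15,400, or 7,700 per arm. In SD units the unadjusted standard error is √(2/7,700) = 0.01612. Then 0.08/0.01612 = 4.964, and power = Φ(4.964 − 1.960) = 99.87%. The stated figure is reproduced, and by an unadjusted comparison.

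**Step 2: effect of baseline adjustment.** ANCOVA multiplies the variance of the arm difference by (1 − r²). The information lost without adjustment is r², and the unadjusted standard error is 1/√(1 − r²) times the adjusted one.

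| r (assumed) | Information lost | Unadjusted SE relative to ANCOVA | Effective number, 15,400 × (1 − r²) | Equivalent women lost |
|---|---|---|---|---|
| 0.4 | 16% | 1.09 | 12,936 | 2,464 |
| 0.5 | 25% | 1.15 | 11,550 | 3,850 |
| 0.6 | 36% | 1.25 | 9,856 | 5,544 |

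**Step 3: whether it changes power.** Power = Φ(SMD/SE − 1.960), with SE = √(1 − r²) × √(2/n per arm).

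| Setting | Unadjusted | r = 0.4 | r = 0.5 | r = 0.6 |
|---|---|---|---|---|
| 7,700 per arm, SMD 0.08 | 99.87% | 99.97% | 99.99% | >99.99% |
| 7,700 per arm, SMD 0.04 | 70% | 77% | 82% | 87% |
| 1,000 per arm (assumed country), SMD 0.08 | 43% | 50% | 54% | 61% |

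The 95% confidence interval half-width at 7,700 per arm falls from 0.0316 SD to 0.0290, 0.0274 and 0.0253 SD. The SMD of 0.04 and the 1,000 per arm are illustrations, not figures from the plan.

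**Step 4: which parts of the Table 1 sentence conflict.**

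- *Student test, EQ-5D VAS and index at four years:* conflicts with the ANCOVA rule.
- *Proportion test, categorical variables such as single EQ-5D dimensions:* agrees with the unadjusted chi-square or Fisher rule of Appendix 1.
- *Either test, Q8 variables or the baseline time point:* an unadjusted comparison is natural.

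The conflict is therefore confined to the first item.

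**The case against.** The strongest reply is that Table 1 is a summary and Appendix 1 is the analysis plan, so the plan governs and the table is only loosely worded. That may be the intention, but the article states no order of precedence. A reader might equally infer that the specific row overrides the general rule, and the text does not support that either. What stands is that two instructions are printed and nothing says which applies.

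It can also be said that baseline data are not lost, because Appendix 1, section d, plans regression and mixed models for patient-reported outcomes. These could use both EQ-5D measurements. However, quality of life is not among the outcomes named there, so that section does not settle the matter.

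The objection on size is largely right. At the plan's SMD of 0.08 nothing of consequence changes, and the example of 22,000 women is well short of the 85,000 target.

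Three stronger readings are tempting and should not be drawn:

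- *That the proportion test also contradicts Appendix 1.* It does not, because ANCOVA is reserved for quantitative variables.
- *That the list of tests in the Analyses section is a further conflict.* It refers to "appropriate tests to assess differences in groups (e.g. chi-square, Fisher and Student, Q Cochran", which is a list of examples, and the same sentence goes on to regression models.
- *That between-arm tests of socio-economic characteristics should all go.* The Objectives section includes these characteristics among the issues compared between arms, and at four years a difference among respondents could reveal differential attrition, a problem Appendix 1 itself raises.

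One objection qualifies the remedy. The Procedure section places baseline questionnaires before randomisation. The Discussion reports that, after enrolment reopened, only the anxiety and worry scales had to be completed before randomisation, "while the other questionnaires could be completed afterwards, either at the inclusion site or at home". For some women the baseline EQ-5D may therefore not be a pre-randomisation covariate.

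**Conclusion.** The inconsistency is real for the continuous EQ-5D measures and for those only. It concerns consistency and efficiency, not bias: under randomisation the unadjusted Student test is valid. The loss is a fraction r² of the information, 16% to 36% for r of 0.4 to 0.6. That range is an assumption, since the documents supply no correlation. For the overall comparison at an SMD of 0.08 the loss is negligible. It becomes material for effects about half that size and for comparisons within a country, which the sample size section describes as well powered. This is a modest point, worth settling because it costs almost nothing.

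**What to change.** In the objective 3 row of Table 1, state that four-year EQ-5D VAS and index are compared between arms by ANCOVA on arm and baseline EQ-5D, as in Appendix 1. Keep the Student or proportion test for descriptive comparison of the Q8 variables and for categorical variables.

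Record the date on which each baseline EQ-5D form was completed relative to randomisation. Add a sensitivity analysis that adjusts only for forms completed before randomisation, or one that is unadjusted.

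The baseline EQ-5D is already scheduled, so the cost is a change of wording, a completion date and slightly more analysis work.
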